### Sample/participants

2.3

Subjects will be recruited using emails, letters and flyers circulated in a southeastern university, its academic medical center and the surrounding metropolitan area. Email communications will be managed by institutional mass‐email distribution services and will prioritize prospective participants who have expressed an interest in participating to either a participating physician or a recruitment platform such as ResearchMatch, a national health volunteer registry that was created by several academic institutions and supported by the U.S. National Institutes of Health as part of the Clinical Translational Science Award (CTSA) program. Recruitment letters will be mailed to prospective participants who have either expressed interest in the study to their physician or were identified as candidates through chart review. Flyers will be posted throughout the medical center and will adhere to IRB guidelines outlining transparency and undue coercion; furthermore, these flyers will also be posted throughout the surrounding area at community centers and assisted living facilities. Because we are interested in the continuous measure of age, we will enroll 60 subjects to yield a final continuous sex‐balanced stratified sample of adults aged 30–89. We will stratify by age range (to allot 5 males/5 females) to each of six age strata: 30–39, 40–49, 50–59, 60–69, 70–79, 80–89. We will identify females who are pre‐ and post‐menopausal to control for hormone status on psychophysical and neurophysiological pain.

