### Data analysis

2.6

Statistical approaches for the analysis of the psychophysical and neurophysiological data will mirror each other. Age (continuous) and sex (male, female), and a term specifying the interaction of age and sex will be entered into general linear modeling modules in SPSS (psychophysical) and SPM (neurophysiological). We are hypothesizing different patterns of association of age with psycho‐ and neurophysiological data for males and females therefore the interaction term will be the primary effect of interest in these analyses. Main effects of ageing and sex will be tested; however, they will serve as covariates in the primary analyses. All data distributions will be evaluated and transformed as needed to meet the assumptions of the specific statistical methods. All statistical significance tests will maintain Type I error rates (alpha values) of no more than 0.05.

#### Aim 1

2.6.1

The temperature at which JNP, WP, and MP is perceived (Aim 1, Hypothesis 1), and the subject's respective affective rating of the pain (Aim 1, Hypothesis 2) at each sensory level, comprise the key dependent variables for Aim 1. Descriptive and graphical summaries of the temperatures (intensities) and affective (unpleasantness) ratings will be generated at each of the three self‐reported sensory thresholds (JNP, WP, and MP), and for each of the stratified levels of age, to inform linear and possible nonlinear associations of age with the intensity and unpleasantness sensations. Linear mixed effects analysis incorporating robust variance estimation (i.e., generalized estimating equations) will be used to test the hypotheses that for a given self‐reported sensory threshold, temperatures are higher, and ratings of unpleasantness are lower with increasing age. This effect would be indicated by a statistically significant interaction of age level with self‐reported sensory level on the dependent variables (Aim 1, Hypothesis 1: temperature; Aim 1, Hypothesis 2: unpleasantness rating). A statistically significant linear or nonlinear association of age with those variables but no interaction effect will indicate an age effect on temperature and unpleasantness regardless of perceived pain.

#### Aim 2

2.6.2

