#### Sample size estimation

2.6.4

Case/control groups of the size proposed in this research (30 younger adults, 30 older adults) will provide 80% statistical power to detect a difference in outcomes of interest as small as half a standard deviation in the distributions of the observed values. This represents a large difference in terms of the expected control values. Given that this is a preliminary exploratory study, we want to focus on detecting larger effects. For example, assuming that we find that the younger group reports that mild pain is experienced on average at 35°C (*SD* 6°C) with a corresponding unpleasantness rating of mean 9.2 (*SD* 4.0), our group sizes can detect an increase in the temperature level for mild pain in the older group as small as 3°C and a difference in unpleasantness ratings as small as 2 scale points. The same logic will hold for the activation and functional connectivity age group analyses. Using data from previous ageing research (Cole et al., 2006, 2010) we can expect that our control participants may have activation values (as Z scores) with approximate *mean* = 3.81 and *SD* 0.46. Given our proposed sample sizes, a respective case activation mean value of ~4.04 would be statistically significant. Correlations between observed values (e.g., pain, age, depression, anxiety, and activation in an ROI) as small in absolute value as 0.34 will be statistically significant (*p* < .05).

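### Aim 1 turns a non-significant age-by-sensory-level interaction into a finding that the age effect does not depend on pain level, which the test cannot show

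*Protocol article*

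**What the plan says.** The protocol article, section 2.6.1 (Data analysis, Aim 1), gives a two-branch reading of the model for temperature and for unpleasantness at JNP, weak pain (WP) and MP.

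- Branch 1, the hypothesised effect: "This effect would be indicated by a statistically significant interaction of age level with self"-reported sensory level.
- Branch 2, a significant linear or nonlinear age association: "but no interaction effect will indicate an age effect on temperature and unpleasantness regardless of perceived pain".

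No confidence interval, margin or limit on interpretation goes with branch 2. The same section plans descriptive and graphical summaries at each sensory level and for each age stratum.

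Section 2.6 sets the error rate: "All statistical significance tests will maintain Type I error rates (alpha values) of no more than 0.05". Section 2.3 sets the size: "we will enroll 60 subjects". Section 2.6.4 treats these as "30 younger adults, 30 older adults" and says that they "will provide 80% statistical power to detect a difference in outcomes of interest as small as half a standard deviation". That statement concerns a difference between age groups. Section 2.6.4 also gives a threshold for correlations, but no power for any interaction.

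**The concern.** Branch 1 makes the presence of an interaction a matter of statistical significance. The absence of an interaction in branch 2 therefore most naturally means p > 0.05. A non-significant test is compatible with no difference in age effect between levels and also with a sizeable one that the study was too imprecise to detect. The rule treats the two alike.

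At stake is how Aim 1 is reported. An age effect that sits mainly at moderate pain could be written up as holding whatever the pain level. Section 2.6.1 uses this interaction as the deciding test for both Aim 1 hypotheses, so the reading of its null result reaches the conclusions.

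**Working it through.** **1. The plan's own power figure.** None is given for this interaction. The nearest is 80% power for 0.5 SD with 30 v 30. The standard error of a group difference is √(2/30) = 0.258 SD, and 0.5/0.258 = 1.94. Two-sided power at 0.05 is Φ(1.94 − 1.96) ≈ 49% (61% one-sided), so the 80% does not reproduce. That is a separate matter, but it means the figure gives no reassurance about a harder comparison.

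**2. Inputs for the interaction.**
- From the document: N = 60, ages 30–89, three levels per subject, alpha 0.05 (two-sided assumed), and a half-SD effect size (3°C with SD 6°C; 2 points with SD 4.0).
- Assumed: one subject at each year of age, equal SD at each level, the same correlation ρ between any two levels, a linear age effect, and no adjustment for sex. The document does not give ρ, so a range is shown.

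**3. Precision of the MP-minus-JNP slope difference.** The sum of squares of age is 60 × (60² − 1)/12 = 17,995. Per 30 years, one unit of residual SD gives a standard error of 30/√17,995 = 0.2236. For the difference between two levels:

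SE = 0.2236 × √(2(1 − ρ)) SD per 30 years.

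**4. Tests.** Let the age effect be 0.25, 0.50 and 0.75 SD per 30 years at JNP, WP and MP, a spread of 0.5 SD.
- 1-df contrast: non-centrality 0.5/SE, t with 58 df.
- 2-df test over three levels: λ = 2 × 0.25² / (0.2236² × (1 − ρ)), F with 2 and 56 df.

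| ρ | SE | 0.5/SE | Missed, 1 df | λ | Missed, 2 df |
|---|---|---|---|---|---|
| 0.5 | 0.224 | 2.24 | 41% | 5.0 | 52% |
| 0.7 | 0.173 | 2.89 | 19% | 8.3 | 29% |
| 0.8 | 0.141 | 3.54 | 6% | 12.5 | 12% |
| 0.9 | 0.100 | 5.00 | <1% | 25.0 | <1% |

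**5. Smaller differences.** With a spread of 0.33 SD (0.33, 0.50, 0.67; MP twice JNP), the 2-df test misses 76%, 63%, 47% and 16% at ρ = 0.5, 0.7, 0.8 and 0.9. The 1-df contrast misses 69%, 53%, 36% and 9%.

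**6. What an interval would show.** The 95% CI half-width for the slope difference is about 2.0 × SE: 0.45 SD per 30 years at ρ = 0.5 (0.45 × 6 = 2.7°C; 0.45 × 4.0 = 1.8 points) and 0.28 SD at ρ = 0.8 (1.7°C; 1.1 points). A non-significant result at ρ = 0.5 could therefore leave open a difference close to the half SD that the plan itself treats as worth detecting.

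**The case against.** **The wording may only mean a main effect.** The sentence does not say that the age effect is equal at the three levels, and a reader who infers a claim of equal size goes beyond the text. It can be taken as the usual fallback of interpreting the age term without conditioning on level. This stands in part. But the sentence is set against the interaction branch and states independence from perceived pain, which is more than an averaged effect. If only an average is meant, saying so costs nothing.

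**Level dependence is not a hypothesis.** This stands. The Aim 1 hypotheses in section 2.1.1 concern age and sex, and the model described in section 2.2 predicts changes greater in females, with no gradient over pain levels. A reader might infer from the Background that level-specific age effects are one of the study's questions, because question (b) there mentions the range from JNP to MP. That question is about how ratings map onto brain activation and does not mention age.

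**By-level summaries are planned.** They are, and a strong gradient might be visible in them. They serve to describe the shape of the age association and do not enter the decision rule.

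**The study is exploratory, and a separate analysis plan may exist.** The exploratory label softens the consequence but gives no ground for concluding independence from pain level. The rule is stated outright in the article, so it is not a detail left to another document.

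**Conclusion.** The point holds as one of interpretation, and it is minor. The error needs no assumed figure: a non-significant age-by-level interaction does not show that the age effect is independent of pain level.

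Its size does depend on assumptions. A 0.5-SD difference per 30 years between JNP and MP is missed in about 41–52% of studies at a correlation of 0.5, 19–29% at 0.7 and 6–12% at 0.8. The lower figure is for a 1-df contrast and the higher for a 2-df test; the document does not say which would be used.

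A reader might infer that 60 subjects will often miss any relevant difference. The document does not support that without conditions, because it gives neither the correlation nor the size that counts as relevant. It is so at low to moderate correlation, or for differences smaller than 0.5 SD.

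**What to change.** Replace the last sentence of section 2.6.1 with wording such as:

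> If the age term is significant and the interaction is not, an age effect averaged over the three levels is concluded and no difference between levels has been shown. Age slopes at JNP, WP and MP and the MP-minus-JNP slope difference are reported with 95% CIs, and level dependence is interpreted from those intervals.

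No equivalence margin is required. The document offers no basis for one, and a margin of ±0.25 SD per 30 years (90% CI within it) would rarely be met even with a true difference of zero: about 0%, 0.4%, 10% and 59% of the time at correlations of 0.5, 0.7, 0.8 and 0.9.

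The cost is a change of wording and a few estimates from the model already planned. The small downside is a more cautious conclusion about level dependence.

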Age and sex associations with functional connectivity will be tested using the connectivity (Z) matrices for the relevant ROI for sensory and affective pain regions using the median connectivity value within the network for each subject. Linear regression analyses will be used to assess the age group effect on the overall connectivity values after co‐varying (adjusting) for regional gray matter volume and resting cerebral blood flow (CBF) as measured by pCASL generation software described below. As with the activation analyses, more specific age (years) and sex associations with activation will be assessed within each of the age groups. We will also examine the association of psychophysical data with regional brain connectivity metrics. To correct for multiple comparisons in brain imaging data we will use 3dClustSim (Cox, 1996; Cox & Hyde, 1997; Gold et al., 1998).To calculate the corrected *p* value of the brain signal in a respective ROI. This program uses the intrinsic volume and Monte Carlo simulations set at 10,000 iterations. A corrected voxel size of activation will be provided for each ROI to determine statistical significance. Data distributions will be evaluated and transformed as needed to meet the assumptions of the specific statistical methods and p‐values of 0.05 will be used for all tests.

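### Section 2.6.2 analyses Aim 2 by undefined age groups, contradicting the continuous age, sex and age-by-sex model that section 2.6 declares

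*Protocol article*

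**What the plan says.** Section 2.3 (Sample/participants) gives the reason for the sampling scheme: "Because we are interested in the continuous measure of age, we will enroll 60 subjects to yield a final continuous sex‐balanced stratified sample". The strata, with five men and five women in each, are "each of six age strata: 30–39, 40–49, 50–59, 60–69, 70–79, 80–89".

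Section 2.6 (Data analysis) sets one model for both kinds of outcome, in SPSS for psychophysics and SPM for imaging: "Age (continuous) and sex (male, female), and a term specifying the interaction of age and sex will be entered into general linear modeling modules". It adds: "therefore the interaction term will be the primary effect of interest in these analyses".

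Section 2.6.2 (Aim 2) departs from this. For connectivity: "Linear regression analyses will be used to assess the age group effect on the overall connectivity values", adjusted for regional gray matter volume and resting cerebral blood flow. Then, by analogy with the activation analyses: "more specific age (years) and sex associations with activation will be assessed within each of the age groups". It names no age-by-sex term, does not say what the age groups are, and sets 0.05 for all tests.

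Section 2.6.4 (Sample size estimation) works with 30 younger versus 30 older adults and carries that reasoning over to the age-group analyses of activation and connectivity.

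**The concern.** Sections 2.6 and 2.6.2 describe different models for the same data. Read literally, Aim 2 could be run with age as continuous, in two groups or in six, and with or without the interaction. An analyst could choose among these after seeing the results.

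The choice matters. Grouping a continuous predictor costs power for the age effect. A slope fitted inside one age group sees only that group's narrow age range and a fraction of the sample, so it says little about ageing. Both Aim 2 hypotheses in section 2.1.2 say that the age association is stronger in females, and only an age-by-sex term tests that directly. Repeating tests at 0.05 in each group also adds chances of a false positive. The cluster correction described in section 2.6.2 operates within a region of interest, not across age groups.

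**Working it through.** **The plan's own figure.** Section 2.6.4 gives 80% power for 0.5 SD with 30 v 30. Two-sided, power = Φ(0.5/√(2/30) − 1.96) = Φ(1.936 − 1.960) = 49%. The 80% is not reproduced. That is a separate matter and is not used below.

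**Inputs.** From the protocol: N = 60, ages 30–89, six decades of 10 or two groups of 30, alpha 0.05. Assumed: ages evenly spaced one year apart, a split at 60, a linear age effect, two-sided tests, no covariates. The assumed effect is r = 0.34, a correlation that section 2.6.4 mentions, used here only as a convenient size. A second value, 0.354, shows the sensitivity.

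**Step 1: where the age variance lies.** For k equally spaced years the variance is (k² − 1)/12.
- Full range: (60² − 1)/12 = 299.92.
- Within a 30-year half: (30² − 1)/12 = 74.92, a share of 74.92/299.92 = 25%. The two-group contrast keeps 75%.
- Within a decade: (10² − 1)/12 = 8.25, a share of 8.25/299.92 = 2.8%. The six-group factor keeps 97%, but spends 5 degrees of freedom.

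**Step 2: standard error of a single-group slope relative to the full-sample slope.** The ratio is √(60 × 299.92 / (n × within-group variance)).
- One half, n = 30: √(17,995/2,247.5) = 2.8.
- One decade, n = 10: √(17,995/82.5) = 14.8.

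**Step 3: power for the age effect.** With β² = r²/(1 − r²) = 0.1156/0.8844 = 0.1307, the noncentrality for continuous age is 60 × 0.1307 = 7.84. For a group factor keeping share B it is 7.84 × B/(1 + β²(1 − B)): 5.70 for two groups and 7.60 for six. For one group's slope it is 7.84 × (within share)/(number of groups): 0.98 for a half and 0.036 for a decade. Noncentral F power:

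| Analysis | df | r = 0.34 | r = 0.354 |
|---|---|---|---|
| Continuous age, all 60 | 1, 58 | 79% | 82% |
| Two-group split | 1, 58 | 65% | 69% |
| Six-decade factor | 5, 54 | 49% | 53% |
| Slope inside one half | 1, 28 | 16% | 17% |
| Slope inside one decade | 1, 8 | 5% | 5% |

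**Step 4: age-by-sex, the declared primary effect.** A 4,000-run simulation assumed a sex difference in slope of 0.74 residual SD per SD of age. Power was 80% with continuous age, 65% with two groups by sex, 49% with six groups by sex, 15% inside one half and 5% inside one decade.

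**Step 5: repeated tests.** For one null association tested independently in each group, the chance of at least one false positive is 1 − 0.95² = 10% with two groups and 1 − 0.95⁶ = 26% with six.

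**The case against.** The strongest reply is that section 2.6 already declares the right model for all neurophysiological data, and nothing withdraws it. The age-group regression in section 2.6.2 is written for connectivity. The Abstract calls the resting-state connectivity analyses secondary, and the Aim 2 hypotheses concern activation only. The within-group associations read as a finer follow-up in a study that calls itself preliminary and exploratory and that separates pre- from post-menopausal women. A look within age ranges can have a purpose there, and a single quadratic term cannot show a step change.

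Much of this stands:

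- A reader might infer that grouping throws away most of the age information. The age-group contrast does not: it keeps about 75% of linear age variance with two groups and 97% with six. Only the within-group slopes discard most of it.
- A reader might infer that the age-by-sex question has been dropped for connectivity. The text only fails to name the term, and section 2.6 may be meant to govern.
- The 15-fold standard error, 5% power and 26% figures hold only if the groups are decades. The one section that ties groups to these analyses, 2.6.4, uses two groups of 30, for which the figures are 2.8-fold, about 16% and 10%.

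The conflict itself remains. Section 2.6.2 presents within-group assessment as the approach also taken for activation, and section 2.6.4 refers to age-group analyses of activation. The problem is therefore not confined to connectivity, and the article states incompatible models rather than leaving one to a fuller document.

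**Conclusion.** The point holds as a contradiction between sections 2.3 and 2.6 on one side and sections 2.6.2 and 2.6.4 on the other, made worse by age groups that are never fixed. Compared with about 80% power for continuous age, grouping costs roughly 10 to 15 percentage points with two groups and about 30 with six. Within-group slopes have little power with two groups and essentially none beyond alpha with six. These sizes rest on even age spacing, a linear effect, two-sided tests, no covariates and an assumed effect size; a markedly nonlinear age effect would change the comparison.

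The documents do not support saying that the primary activation analysis has been replaced, since section 2.6 still states it. The point should be corrected, but it does not by itself invalidate Aim 2.

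**What to change.** In section 2.6.2, state one model for both activation and connectivity over all 60 participants: continuous age, sex, age-by-sex, and the gray matter volume and resting cerebral blood flow covariates already listed. One quadratic age term may be added to check curvature, at the cost of one degree of freedom.

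Define the age groups once, and use the same definition in sections 2.3, 2.6.2 and 2.6.4. Label grouped summaries and any within-group associations as descriptive or exploratory, reported as estimates with intervals rather than tested at 0.05. They need not be deleted.

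The change is wording only, needs no new data or participants, and brings Aim 2 back to the protocol's own declared analysis. What is given up is the formal test status of the within-group results.

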#### Missing data

2.6.3

This is a short protocol, with one scan day per participant; therefore, there will be no dropouts after the scan, since the scans complete the necessary procedures. We will ensure sufficient enrollment so that subjects have a full complement of usable scan data.

#### Sample size estimation

2.6.4

Case/control groups of the size proposed in this research (30 younger adults, 30 older adults) will provide 80% statistical power to detect a difference in outcomes of interest as small as half a standard deviation in the distributions of the observed values. This represents a large difference in terms of the expected control values. Given that this is a preliminary exploratory study, we want to focus on detecting larger effects. For example, assuming that we find that the younger group reports that mild pain is experienced on average at 35°C (*SD* 6°C) with a corresponding unpleasantness rating of mean 9.2 (*SD* 4.0), our group sizes can detect an increase in the temperature level for mild pain in the older group as small as 3°C and a difference in unpleasantness ratings as small as 2 scale points. The same logic will hold for the activation and functional connectivity age group analyses. Using data from previous ageing research (Cole et al., 2006, 2010) we can expect that our control participants may have activation values (as Z scores) with approximate *mean* = 3.81 and *SD* 0.46. Given our proposed sample sizes, a respective case activation mean value of ~4.04 would be statistically significant. Correlations between observed values (e.g., pain, age, depression, anxiety, and activation in an ROI) as small in absolute value as 0.34 will be statistically significant (*p* < .05).

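### The sample size paragraph gives power for a younger-versus-older comparison, not for the primary age-by-sex interaction, and its 80% is wrong even for that comparison

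*Protocol article*

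**What the plan says.** - **Primary effect.** Section 2.6 (Data analysis) enters continuous age, sex and their interaction, and reasons that the sexes are expected to show different age patterns, "therefore the interaction term will be the primary effect of interest in these analyses". Main effects are to be tested but act as covariates in the primary analyses. The four hypotheses in section 2.1 each predict an age association in females that is weaker in males.
- **Sample.** Section 2.3 states: "Because we are interested in the continuous measure of age, we will enroll 60 subjects". Five men and five women are allotted to each of six age decades, which makes 30 per sex.
- **Power.** Section 2.6.4 (Sample size estimation) bases its claim on "Case/control groups of the size proposed in this research (30 younger adults, 30 older adults". For that comparison it promises 80% power at a difference of half a standard deviation. Its examples are all 0.5 SD: 3°C at SD 6°C, 2 points at SD 4.0, and an activation mean of about 4.04 against 3.81 at SD 0.46. It adds that correlations as small as 0.34 will be significant. Sex does not appear in the paragraph.
- **Alpha.** Section 2.6: "All statistical significance tests will maintain Type I error rates (alpha values) of no more than 0.05". Sidedness is not stated.

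**The concern.** The planning claim and the primary analysis concern different contrasts. The claim covers a mean difference between two age groups with the sexes pooled. The primary effect is the difference between women and men in the slope on age. An interaction is estimated less precisely than the matching main effect in the same people, so the detectable size cannot be carried over from one to the other.

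A reader of section 2.6.4 would take half-SD effects to be within reach for the main question, and could then give a non-significant interaction more weight than it can bear. Section 4 (Conclusion) looks ahead to pain management tailored to age and sex if the hypotheses are borne out, so what this sample can and cannot resolve should be stated correctly.

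**Working it through.** **Inputs.** From the protocol: n=60, 30 per sex, 30 younger and 30 older; alpha 0.05; SDs 6°C, 4.0 points and 0.46 activation units. Assumed: two-sided tests, residual SD equal to the quoted SD and the same in both sexes, one pain level analysed, ages spread evenly over 30–89.

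**1. The plan's own figure (30 versus 30, 0.5 SD, 80% power).**
- SE of the difference = SD × √(2/30) = 0.258 SD.
- Noncentrality at 0.5 SD = 0.5/0.258 = 1.94. Power from the noncentral t on 58 df = 48% (normal approximation 49%).
- A one-sided 0.05 test gives 61%. The 80% is not reproduced either way.
- Detectable difference at 80% power = 2.849 × 0.258 = 0.74 SD, which is 4.4°C, 2.9 points or 0.34 activation units.
- For 80% power at 0.5 SD, 63 per group would be needed (normal approximation).
- A possible source of the 0.5 SD is the smallest *observed* difference that reaches p<0.05: 0.51 SD (normal) or 0.52 SD (t). A true difference of that size has only about even odds of reaching significance.

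**2. Interaction in the same two-group framing (age half × sex, 15 per cell).**
- SE of the difference of differences = SD × √(4/15) = 0.516 SD, twice the 0.258 above.
- Detectable at 80% power, t on 56 df = 2.851 × 0.516 = 1.47 SD, which is 8.8°C, 5.9 points or 0.68 activation units.
- Ratios: 1.47/0.74 = 2.0 against the corrected main-effect figure; 1.47/0.5 = 2.9 against the printed one.
- Power for a 0.5 SD difference of differences = 16%.

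**3. Interaction with age continuous, as section 2.6 specifies.**
- Ages spread evenly over the range have SD about 17.3 years, so the sum of squares per sex is about 30 × 17.3² ≈ 9,000.
- SE of the slope difference = SD × √(2/9,000) = 0.0149 SD per year, or 0.149 SD per decade.
- Detectable slope difference = 2.851 × 0.149 = 0.425 SD per decade. Other ways of placing ages within decades give 0.42 to 0.43; about 0.43 is used below.
- In units: 0.43 × 6 ≈ 2.6°C, 0.43 × 4.0 ≈ 1.7 points and 0.43 × 0.46 ≈ 0.20 activation units per decade.
- The detectable common slope on age is 0.21 SD per decade, so the ratio is again 2.0.

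**4. Power for some assumed interactions** (simulated; correlation of outcome with age in women versus men; the protocol gives no expected values).

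| Women vs men | Equal residual SD | Equal total SD |
|---|---|---|
| 0.60 vs 0 | about 82% | about 72% |
| 0.50 vs 0 | 59% | about 53% |
| 0.34 vs 0 | 28% | about 27% |
| 0.50 vs 0.25 | 23% | 18% |

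**The case against.** **The study is preliminary and exploratory, and aims at larger effects.** Sections 2.6.4 and the abstract say so. This lowers the stakes, but the paragraph still asserts 80% power, and a primary effect is still named and tested at 0.05.

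**Grouped-age comparisons are part of the plan.** This stands. The Aim 2 analysis text tests an age group effect on connectivity and looks within age groups, so it would be wrong to say that the study has no age groups. Main effects will also be tested, and section 2.6.1 frames the Aim 1 test as age with pain level, without a sex term. The two-group figure therefore has some use, but it does not serve the effect that section 2.6 calls primary, and it needs correcting anyway.

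**A second planning figure uses continuous age.** The correlation of 0.34 does list age among its variables. It concerns a single correlation, not a difference between the sexes.

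**Repeated pain levels and covariates add precision.** They may, and the detectable effects would then shrink. If they reduce the error for the main effect and the interaction by the same factor, the ratio of two is unchanged.

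**A stronger reading.** A reader might infer that the interaction would be missed most of the time. The protocol does not support this. It states no expected interaction size, and its pilot account (section 3) describes an association in females only. Under such a pattern, power passes one half once the correlation in women reaches about 0.50. Nor does any section plan to read non-significance as absence of a sex difference.

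**Conclusion.** The concern holds as a mismatch between sections 2.6 and 2.6.4, together with a wrong power figure. The printed 80% at 0.5 SD does not apply to the primary interaction, and for 30 versus 30 the power is about 48%, with 0.74 SD needed for 80%. The detectable interaction is twice that 0.74 SD: 1.47 SD as a difference of differences, or about 0.43 SD per decade of age. The factor of two is against the corrected main-effect figure; against the printed 0.5 SD it is 2.9.

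The power and detectable-effect figures depend on the assumptions listed in the working. In particular, the 6°C and 4.0 are illustrative values for the younger group, used here as residual SDs over the whole age range. The mismatch itself depends on none of these assumptions. It does not show that n=60 is unsuitable for an exploratory study.

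**What to change.** Keep n=60 and restate section 2.6.4.

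1. Correct the two-group figure: 80% power for about 0.74 SD, or about 48% power for 0.5 SD. Change the 3°C, 2-point and 4.04 examples to match, and drop the case/control label, since all participants are healthy adults.
2. Add the figure for the primary test, for example:

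> With 30 women and 30 men spread evenly over ages 30–89, there is 80% power (two-sided 0.05) for an age-slope difference between the sexes of about 0.43 residual SD per decade (about 2.6°C, 1.7 unpleasantness points or 0.20 activation units per decade). This assumes that the residual SDs equal the quoted SDs (6°C, 4.0, 0.46) and are equal in both sexes, and that a single pain level is analysed without gain from repeated levels or covariates.

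3. State that the interaction will be reported as an estimate with a 95% confidence interval, and that a non-significant interaction is not evidence of equal slopes.

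The cost is rewording only; recruitment, procedures and analysis model are untouched. The drawback for the sponsor is that the stated detectable effect becomes less favourable.
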